### ***Blood sampling***

Blood donations are generally very safe and side effects are rare. Pain and bruising may occur at the needle placement sites. As with other kinds of blood drawing, temporary lowering of the blood pressure may develop, and light-headedness, dizziness and even fainting may result. Trained study Investigators or stroke research nurses at The Florey, Sunshine Hospital, or The Alfred Centre will perform the blood draw and preliminary processing. Sterilized, single-use equipment will be used to draw blood and is disposed of following a donation procedure. Blood drawing equipment is never in contact with blood from another individual. No blood products are given during these procedures. Medical doctors are available at all times during the donation procedure to provide short-term medical care for any complications or reactions resulting from donation procedure.

## **b. ADVERSE EVENT MANAGEMENT**

Investigators will complete an 'Adverse Event Case Report Form' to detail and monitor any cases of adverse events occurring within the study.

At each exercise session between two and four months post-stroke, and at the second and third visits (four and 12 months post-stroke, respectively), participants will be assessed for possible Adverse Events (AEs). AEs will be reported as they occur in the participant's CRF.

AEs that meet the criteria for serious, are considered Serious Adverse Events (SAEs) and will be reported for each participant for the duration of their participation in the study (i.e., between two months and 12 months post-stroke). The investigator or designee will ask the participant non-leading questions in an effort to detect adverse events, and serious adverse events.

### ***Definition of an Adverse Event (AE)***

An Adverse Event (AE) is any untoward medical occurrence in any participant involved in the study. It does not necessarily have to have a causal relationship to the study intervention.

Examples of an AE include:

- Exacerbation of a chronic or intermittent pre-existing condition including either an increase in frequency and/or intensity of the condition.
- New conditions detected or diagnosed after involvement in the study even though it may have been present prior to the start of the study.

### ***Definition of a Serious Adverse Event (SAE)***

- A serious adverse event is any AE that:
  - a) results in death
  - b) is life threatening
    - Note: The term 'life-threatening' in the definition of 'serious' refers to an event in which the participant was at risk of death at the time of the event. It does not refer to an event, which hypothetically might have caused death if it were more severe.

- c) requires hospitalisation or prolongation of an existing hospitalisation.
  - Note: In general, hospitalisation signifies that the participant has been detained (usually involving at least an overnight stay) at the hospital or emergency ward for observation and/or treatment that would not have been appropriate in the physician's office or out-patient setting. Complications that occur during hospitalisation are AEs. If a complication prolongs hospitalisation or fulfils any other serious criteria, the event is serious. When in doubt as to whether 'hospitalisation' occurred or was necessary, the AE will be considered serious.
  - Hospitalisation for elective treatment of a pre-existing condition that did not worsen from baseline is not considered an AE.
- d) results in disability/incapacity
  - Note: The term disability means a substantial disruption of a person's ability to conduct normal life functions. This definition is not intended to include experiences of relatively minor medical significance such as uncomplicated headache, nausea, vomiting, diarrhoea, and influenza, which may interfere or prevent everyday life functions, but do not constitute a substantial disruption.

Medical and scientific judgement will be exercised in deciding whether reporting is appropriate in other situations, such as important medical events that may not be immediately life-threatening or result in death or hospitalisation, but may jeopardise the participant or may require medical or surgical intervention to prevent one of the other outcomes listed in the above definition. These will also be considered serious. Examples of such events are invasive or malignant cancers, intensive treatment in an emergency room or at home for allergic bronchospasm, blood dyscrasias or convulsions that do not result in hospitalisation, or development of drug dependency or abuse.

The investigator will exercise his or her medical and scientific judgement in deciding whether an abnormal laboratory finding or other abnormal assessment is clinically significant.

### ***Time Period, Frequency, and Method of Detecting AEs and SAEs***

All AEs and SAEs will be recorded from the time of consent until the final follow up visit at one year post-stroke. Each participant will be monitored regularly by the investigator and study personnel for events occurring throughout the study.

During the study, the investigator will enquire about AEs by asking the following non-leading questions:

*"How are you feeling?"*

At subsequent scheduled intervals participants will be asked:

*"Since you were last asked, have you felt unwell or different from usual?"*

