## **VIII. Fitness test of aerobic capacity – VO2 peak graded exercise test (GXT)**

Aerobic capacity will be repeatedly assessed at each study visit via a submaximal, incremental exercise test. At the initial Baseline visit, information from the GXT will also be used to create each participant's graduated exercise programme.

All participants will undergo a  $VO_{2peak}$  graded exercise stress test to determine exercise capacity using a metabolic cart (the Oxycon mobile™, CareFusion). A submaximal GXT will be conducted at each of the three study visits to monitor the change in aerobic capacity. The GXT will take place at the Florey, Melbourne Brain Centre, Austin campus, or in the AIMSS facility at Western Health, under the supervision of a trained exercise professional. This person will not be involved with the exercise training as they are not blinded to participant status.

The following parameters will be recorded during the test:  $VO_{2peak}$  (volume oxygen uptake in ml/kg/min), Heart Rate (HR), Heart Rate Reserve (HRR, subtracting resting heart rate from the maximum heart rate measured during an exercise test), Oxygen Saturation, and Respiratory Rate (RR, number of breaths per minute). These parameters will enable us to derive  $VO_{2peak}$  as an estimate of aerobic exercise capacity. Blood pressure and ECG recordings will be monitored as markers of participant well-being.

A total body recumbent stepper will be used to perform the GXT, as outlined by Billinger [32]. This submaximal GXT protocol has been shown to be a valid measurement of  $VO_{2peak}$  [35], and prescribing cardiorespiratory exercise based on  $VO_{2peak}$  values is safe in a subacute stroke population with mild to severe post-stroke deficits [36].

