## **IX. Physical activity monitoring**

Physical activity and energy expenditure will be monitored by an Actiwatch Spectrum Plus (Koninklijke Philips, Amsterdam, Netherlands). The Actiwatch is a small, unobtrusive electronic physical activity monitor on an adjustable wrist strap that is worn on the left wrist. If participants have left-arm paresis the monitor will be fitted to the right wrist. Participants will be asked to wear the waterproof Actiwatch 24 hours per day for 7 days. In previous studies, conducted by the current Investigators, involving the use of Actiwatches for the duration specified there have been no complaints or concerns raised by participants.

The Actiwatch will be fitted onto participants at each of the three timepoints throughout the study, after the MRI scan and cognitive testing has been completed. Following the 7 day monitoring period, participants will be asked to return the de-identified Actiwatch in a de-identified pre-paid envelope to the study investigators.

In addition, participants will be asked to keep a daily activity diary that records participant activity levels between assessment visits. Such diaries are common place as a part of general post-stroke rehabilitation programmes and this is not expected to be an inconvenience for participants.

Time spent active will be used as a co-variate for data analysis.

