### ***Cardiovascular events or respiratory events as a result of physical exercise***

Although rare, two common cardiac risks include myocardial ischemia and different forms of arrhythmias. It is estimated that for adults without existing heart disease, the risk of a cardiac event or complication ranges between 1 in 400,000–800,000 hours of exercise. For patients with existing heart disease, an event can occur on average of once in 62,000 hours [43]. The exercise tests and training also involve a risk of vasovagal episodes.

To mitigate the risk of a vasovagal episode or any other significant adverse cardiac event, all participants must be cleared by a consulting physician before commencing the exercise test and exercise training intervention. The exercise testing and training will be in accordance with current guidelines from the ACSM Exercise Testing and Prescription (ACSM, 2013). [name] (Associate Investigator) is experienced in conducting exercise tests and prescribing exercise and will be responsible for training staff involved in the exercise component of the study.

This study is employing a submaximal, graded exercise test, and the exercise intervention includes CRF training at 50 to 75% of the participant's maximal aerobic capacity. It is not anticipated that the participants will be exercising at an intensity that is likely to induce significant adverse events.

Irrespective, the participant will be closely monitored at all times during the exercise test and during the exercise intervention. Participants will be required to nominate somebody the research team can contact in case of emergency during the exercise intervention. This person may also be involved as a study partner and need to attend each of the exercise intervention sessions if the Exercise Professional deems it necessary. All investigators involved in the exercise testing are required to maintain current first aid qualifications.

Participants will be educated about the procedure to follow should any concerning cardiovascular signs or respiratory signs occur off-site (i.e., not at the Austin Health campus, Eastern Health campus, Western Health campus, or The Alfred Centre ) whilst enrolled in the study. Participants will be provided with a 'Participant Adverse Event Notification Form' to document events and notify Investigators.

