### ***Physical injury as a result of physical exercise***

All exercise procedures involve some risk to participants. It is possible that the participants will experience muscle soreness and stiffness as a result of completing the exercise tests and training. Such feelings are likely to subside within 24 to 48 hours after the exercise and leave no sustained muscle damage.

If participants raise concern about a physical injury sustained while participating in the study then these will be assessed by [name] (Senior Research Exercise Physiologist) or another member of the research team with appropriate training (medical doctor [e.g., [name] or [name]] or physiotherapist [e.g., [name]]).

Appropriate diagnosis and treatment will be arranged, without monetary cost to the participant, through the health service from which they were recruited.

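### Adverse-event recording closes at the 12-month visit, although that visit includes the last exercise test and study procedures run on for about a week

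*Protocol*

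**What the plan says.** **Recording window.** Protocol Section 7.b, under the heading on time period, frequency and method of detection, says: "All AEs and SAEs will be recorded from the time of consent until the final follow up visit at one year post-stroke". The opening part of 7.b gives a second window, for serious events only: "reported for each participant for the duration of their participation in the study (i.e., between two months and 12 months post-stroke". The two statements close at the same point but open at different ones (consent; two months after stroke).

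**Last enquiry.** Adverse events are assessed at each exercise session, and then "at the second and third visits (four and 12 months post-stroke, respectively), participants will be assessed for possible Adverse Events (AEs". No later contact for collecting events is described. The follow-up paragraph of 7.b returns only to events that are already documented and still ongoing.

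**Last exercise exposure.** Section 5.d.VIII: "A submaximal GXT will be conducted at each of the three study visits to monitor the change in aerobic capacity". The procedures table in Section 5.b confirms a test at one year, lasting 30 to 60 minutes.

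**Expected after-effect.** Section 7.a says that both the tests and the training may cause soreness and stiffness: "Such feelings are likely to subside within 24 to 48 hours after the exercise".

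**After the visit.** Section 5.d.IX: "Following the 7 day monitoring period, participants will be asked to return the de-identified Actiwatch in a de-identified pre-paid envelope". Sections 5.b, 5.d.X and 5.d.XII place the sleep diary and a 3-day food diary in the week after each timepoint, including the last.

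**Participant reporting.** Section 7.a, on off-site cardiovascular or respiratory signs during enrolment: "Participants will be provided with a 'Participant Adverse Event Notification Form' to document events and notify Investigators".

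**The concern.** A safety window would normally run past the last study exposure long enough to see the effects that the protocol itself expects. Here the stated end of recording is the same visit that contains the last exercise test. The first two tests do not have this problem. The baseline test is followed by an enquiry at every exercise session, and the 4-month test by the enquiry at 12 months. After the third test nobody is scheduled to ask again.

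There is also a mismatch inside Section 7.b. It describes the serious-event window as the length of participation, yet participants are still carrying out study procedures for about a week after the window shuts. At stake is complete harm reporting after the third test: mainly mild musculoskeletal events, and in principle a rare serious event starting after the visit, which on the stated wording would not be a recorded study event.

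**Working it through.** The plan states no figure that needs reproducing. The check sets the timings side by side and then sizes the gap.

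**1. How much of the post-test period is uncovered?**

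Inputs:
- Soreness and stiffness expected for up to 48 hours after exercise (Section 7.a).
- Each visit has two parts. The blood pressure monitor is fitted at the first and returned at the second (Section 5.a), and it is worn for 24 hours (Section 5.d.V). The parts are therefore about 24 hours or more apart.
- No section says which part holds the exercise test.

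Assumption: the final visit ends with its second part.

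Uncovered hours = 48 − min(48, hours from the test to the end of the visit).

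| Place of the third test | Gap between parts | Uncovered hours |
|---|---|---|
| Second part | any | 48 − 0 = 48 |
| First part | 24 h | 48 − 24 = 24 |
| First part | 48 h or more | 48 − 48 = 0 |

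The range is 0 to 48 hours, and the protocol does not fix where in it the trial will lie. Events during the test, or before the visit ends, are inside the window in every case.

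**2. How many tests are affected?**

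Up to 120 participants. With the 30% attrition assumed in Section 8.b, 120 × (1 − 0.30) = 84.

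**3. How many cardiac events go with the third test?**

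Expected events = participants × hours per test × rate per hour. Section 7.a gives 1 per 62,000 exercise hours with existing heart disease and 1 per 400,000 to 800,000 hours without.

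- 120 × 0.5 h = 60 h; 120 × 1 h = 120 h.
- With heart disease: 60/62,000 = 0.0010 to 120/62,000 = 0.0019.
- Without: 60/800,000 = 0.00008 to 120/400,000 = 0.0003.
- With 84 attending, the highest figure is 84/62,000 = 0.0014.

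These count every cardiac event tied to the test at those rates. Events that occur during the test are recorded, so the number that could be missed is no larger.

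**4. What share of exercise exposure is this?**

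The intervention has 3 × 8 = 24 supervised sessions of one hour, with events assessed at each. With three tests of 0.5 to 1 hour, there are 24 + 3 = 27 exposures and 25.5 to 27 hours. The third test is 1 of 27 exposures, and 0.5/25.5 = 2% to 1/27 = 4% of the hours.

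**5. Does another provision close the gap?**

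- Follow-up of documented events does not cover an event that is new after the visit.
- The notification form covers off-site cardiovascular or respiratory signs during enrolment, but the end of enrolment is not defined beyond 12 months after stroke.

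**The case against.** The strongest reply is that ending collection at the last visit is an ordinary design choice, that the two statements in Section 7.b agree on the closing point, and that what may be lost is mostly expected, self-limiting soreness. Participants are monitored throughout the test, the notification form is available, and injury concerns raised by a participant are assessed with no stated cut-off. Test safety is not among the listed aims or outcomes. The third test comes about 8 months after the intervention ends and is the same in both arms.

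Most of this stands, and it limits the size of the point. It does not remove it: the same document expects an after-effect of the last test, keeps participants under study procedures for a further week, and tells staff to stop recording before either is over. The form and the injury assessment are partial routes, because a later event would still fall after the stated end of recording.

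Two stronger readings are tempting, and the documents support neither:
- A reader might infer that the whole post-test period of one test in three is lost, so that test-related harms are undercounted by a third. That needs the test to fall in the second part of the visit, equal risk at all three tests, and no events captured during the test. The first is not stated. Equal risk is doubtful, because the stopping criteria in Section 5.d.VIII exclude some participants. Events during the test are recorded.
- A reader might apply the 24 to 48 hours to cardiac events or injury. Section 7.a gives that period only for soreness and stiffness.

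**Conclusion.** The point holds in a limited form. As written, adverse events and serious adverse events that begin after the 12-month visit are not recorded, although that visit contains the last exercise test and participation continues for about a week. Between 0 and 48 hours of the period in which soreness or stiffness is expected lies outside the window, in up to 120 participants, or about 84 with the planned attrition.

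The consequence is small. The gap is the same in both arms, so it does not bias the comparison between them. The 4-month primary outcome is untouched. Expected cardiac events tied to the third tests are at most about 0.002, which rests on the protocol's quoted rates and on a test of no more than one hour. The range of uncovered hours rests on taking the second part as the end of the visit and on a gap of at least 24 hours between the parts. The change is still worth making, because following the text exactly would leave out a new event after the last exposure and avoiding that costs little. Separately, the two opening dates for serious events cannot both apply.

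**What to change.** Reconcile the two recording statements in Section 7.b with the test schedule (5.b, 5.d.VIII), the activity monitoring (5.d.IX) and the expected after-effects (7.a). In both statements, end recording of adverse events and serious adverse events when the 12-month Actiwatch is returned, about 7 days after it is fitted. Have the participant put the existing notification form, with an option to report no event, into the same pre-paid envelope. In the same edit, give the serious-event window one opening point, since one statement says consent and the other two months after stroke. This changes data capture only; it alters no test, treatment or stopping rule.

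The cost is a short amendment to Section 7.b and one existing form in an envelope that is already being posted. Each participant's safety window closes about a week later. Some forms may not be returned, so the plan should say how a missing form is handled, rather than letting it count as no event.

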### ***Recording of AEs and SAEs***

1221 When an AE/SAE occurs, the investigator will review all documentation (e.g. hospital  
1222 progress notes, laboratory, and diagnostic reports) relative to the event. The investigator will  
1223 then record all relevant information regarding an AE/SAE in to the CRF.

1224 For each reportable event, start and stop dates, action taken, outcome, intensity and  
1225 relationship to study treatment (causality) will be documented. If an AE changes in frequency  
1226 or intensity during a study, a new entry of the event will be made.

1227 The investigator will attempt to establish a diagnosis of the event based on signs, symptoms,  
1228 and/or other clinical information. In the absence of a diagnosis, the individual  
1229 signs/symptoms will be documented.

1230 All details of any treatments initiated due to the adverse event will be recorded in the  
1231 participant's notes and the CRF.

1232 The investigator will notify the Ethics Committee of any SAEs once per year in the annual  
1233 progress report.

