### Recruitment

Our experience from the CANVAS and other imaging stroke studies suggest that around 30-40 stroke participants can be recruited into an intensive imaging study over a 1 year period.

A pre-study assessment questionnaire will be completed to determine eligibility in the study. This assessment addresses very broad aspects of MRI eligibility (e.g. pacemaker or severe claustrophobia). Informed consent will then be obtained from participants before any

participation in the study protocol. A thorough MRI-safety screening questionnaire will then be used. This will involve the collection of demographic information (e.g., name, address, contact phone number), medical information (e.g., previous medical operations and procedures, inserted devices, cardiovascular function, respiratory complications, current medications) and psychiatric information (e.g., previous diagnoses). This information will be collected to ensure that participants have no contraindications for MRI and are suitable for the study.

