### Exercise groups and programmes

For ease of intervention and to increase accessibility and recruitment, the exercise intervention will be offered as a telehealth model. Both groups will undertake an 8-week exercise programme. Participants will partake in 1 hour-long exercise sessions, three-times per week, for 8 weeks. These sessions will be run by a trained exercise professional (e.g., Exercise Physiologist, Physiotherapist, or Research Assistant trained in exercise prescription). Training will be provided by [name] (Associate Investigator and Senior Research Exercise Physiologist). The exercise programme will be conducted in the individuals' homes, whilst the exercise professional monitors and facilitates the session via Zoom or other videoconferencing programs. When possible, the participants' exercise preferences will be considered when designing their individual exercise program.

To ensure optimal levels of safety are achieved whilst completing home based interventions, a home visit will be completed prior to commencing the intervention. This home visit will be conducted by the exercise professional, in collaboration with Occupational Therapists and clinical specialists with extensive safety assessment experience, if required. The visit will be used to assess the safety of the area the participant will be exercising in and minimise any potential risks. Additionally, the home visit will determine if the participant requires a 'study partner' to be at home with them throughout the duration of the session, should they need help.

An exercise intervention 'pack' will be delivered to participants after the first time-point assessment. These packs will consist of everything required to complete the exercise intervention as usual, such as monitoring (HR monitors), safety assessments (blood pressure) and exercise equipment (i.e. bikes, cones, step, stopwatch). After the participant has finished the 8 week intervention, all equipment will be thoroughly cleaned prior to being

utilised again. Exercise equipment will be stored in secure locations within the Melbourne Brain Centre, AIMSS facility, and The Alfred Centre between participant use.

To ensure blinding is maintained, only Exercise Professionals will liaise with the participants regarding all organisation of home visits and equipment deliveries. Larger equipment required to complete the intervention such as bikes, will be professionally delivered to ensure OHS protocols are followed.

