## 6. STUDY POPULATION

### a. RECRUITMENT PROCEDURE

120 newly acquired ischaemic stroke participants (i.e., <2 months post-ischaemic stroke) will be recruited from the Austin Health, Eastern Health, Western Health, and Epworth Camberwell Stroke Units and followed longitudinally. All ischaemic stroke subtypes will be included. Several methods will be used to recruit participants over the 3 year recruitment period of the study:

- a) The Principal Investigator ([name]) holds clinical appointments at both Austin Health and Eastern Health Stroke Units.
- b) Senior clinicians on all Stroke Units will be notified of the study and asked to identify potentially suitable participants.
- c) Study investigators will attend ward rounds and clinical meetings to identify potentially suitable participants.

In each case of the above, potential participants will be approached with the guidance of [name] or the senior inpatient ward clinician. The study investigators will speak to potential participants and provide them with verbal and written information on the study.

Participants will be screened to ensure that they are cognitively able to participate in the study and have no contraindication to the MRI. The investigators will screen potential participants using a short, semi-structured questionnaire. If the recruiter is unsure whether the potential participant has the cognitive capacity to participate, the opinions of the study neuropsychologist will be obtained.

Demographic and medical information including age, gender, medication status, side and site of stroke and admission stroke severity (National Institutes of Health Stroke Scale, NIHSS) and functional status (modified Rankin Score, mRS) will be obtained.

1001                   b. INCLUSION CRITERIA

1002 120 participants who recently acquired ischaemic strokes (i.e., ischaemic stroke <2 months)  
1003 will be recruited. All ischaemic stroke subtypes will be included.

1004  
1005 Participants will be included if the following eligibility criteria are met during the initial  
1006 screening:

- 1007 • Ischaemic clinical stroke patient (first or recurrent stroke) aged greater than 18 years;
- 1008 • Cardiac function not precluding exercise intervention;
- 1009 • Premorbid mRS<3, denoting no, mild or moderate disability; and
- 1010 • Able to give consent; and
- 1011 • Able to nominate an emergency contact person.

1012                   c. EXCLUSION CRITERIA

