#### 1247 ***Assessment of Causality***

1248 A blinded assessor will assess the relationship between study treatment and the occurrence  
1249 of each AE/SAE. The blinded assessor will use clinical judgment to determine the  
1250 relationship. Alternative causes, such as natural history of the underlying diseases,  
1251 concomitant therapy, other risk factors, and the temporal relationship of the event to the  
1252 treatment period will be considered.

1253 The causal relationship to the study treatment will be assessed using the following  
1254 classifications:

1255 Not Related In the Assessor's opinion, there is not a causal relationship between the study  
1256 product and the adverse event.

1257 Unlikely The temporal association between the adverse event and study treatment is  
1258 such that the study treatment is not likely to have any reasonable association  
1259 with the adverse event.

1260 Possible The adverse event could have been caused by the study treatment.

1261 Probable The adverse event follows a reasonable temporal sequence from the time of  
1262 study treatment, abates upon discontinuation of treatment and cannot be  
1263 reasonably explained by the known characteristics of the study participant's  
1264 clinical state.

1265 Definitely The adverse event follows a reasonable temporal sequence from the time of  
1266 study treatment start or reappears when study treatment is reintroduced.

1267 ***Assessment of Expectedness***

1268 **Expected** An adverse event, the nature or severity of which is consistent with the clinical  
1269 condition of the participant.

1270 **Unexpected** An adverse event, the nature or severity of which is not consistent  
1271 with the clinical condition of the participant.

1272 ***Follow-up of AEs and SAEs***

1273 All AEs and SAEs documented at a previous visit/contact and are designated as ongoing,  
1274 will be reviewed at subsequent visits/contacts.

1275 All AEs and SAEs will be followed until resolution, until the condition stabilises, until the  
1276 event is otherwise explained, or until the participant is lost to follow-up.

1277 New or updated information will be recorded on the originally completed SAE form, with all  
1278 changes signed and dated by the investigator.

1279

1280 **c. HANDLING OF WITHDRAWALS**

1281 If a participant experiences some distress as a result of participation in the study, and  

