## 8. STATISTICAL METHODS

#### a. SAMPLE SIZE ESTIMATION & JUSTIFICATION

We aim to recruit 120 participants who have experienced ischaemic stroke in the past 2 months. We calculate 60 participants per group are required. We calculated our sample size (see Section 8.b.) in order to include sufficient participant numbers for estimation of the primary endpoint: brain volume at 4 months post-stroke.

Methods of participant recruitment are detailed in Section 6.a.

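### Section 7.b sends every serious adverse event, related or not, to the Ethics Committee only once a year, and no causality grade triggers a faster report

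*Protocol*

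**What the plan says.** Section 7.b (Recording of AEs and SAEs) contains the only statement of who outside the study team is told of an SAE, and when: "The investigator will notify the Ethics Committee of any SAEs once per year in the annual" progress report. It covers all SAEs alike.

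The same section collects the information that a faster rule would need. The investigator grades intensity. A blinded assessor places each event in one of five causality categories, from not related to definitely related. Expectedness is also classified, with an expected event defined as "An adverse event, the nature or severity of which is consistent with the clinical" condition of the participant. No recipient, deadline or action is attached to any of these grades.

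Within the team, detection is well covered:
- Section 5.b (Exercise groups and programmes) has an exercise professional running each home session live by videoconference. A study partner is in the home where this is judged necessary.
- Section 7.a says participants are kept under observation throughout the exercise tests and sessions, and gives them a form for notifying investigators of events.
- Section 7.b has adverse events asked about at each session and at the 4- and 12-month visits, and has the investigator review the records when an event occurs.

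**The concern.** Safety reporting belongs in the protocol, and here it is fixed by an explicit sentence that site staff would follow. Followed literally, a death during a session that the assessor calls definitely related to the exercise travels to the Ethics Committee on the same timetable as an unrelated admission. The causality assessment is done and then changes nothing.

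The trial recruits at several hospitals, in people within months of a stroke, and the exercise takes place without study staff on site. Section 7.a itself names cardiovascular events as a risk of the intervention. If a related SAE occurs, the committee that oversees the trial, and investigators at the other sites, may not know of it while further participants are consented and randomised to the same programme. What is at stake is timely outside review. The primary brain-volume analysis is not affected.

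**Working it through.** **Inputs**
- Sample size 120 (Section 8.a): "We aim to recruit 120 participants who have experienced ischaemic stroke in the past 2 months".
- Recruitment period 3 years (Section 6.a): "Several methods will be used to recruit participants over the 3 year recruitment period of the study".
- Recruitment pace from earlier studies (Section 5.a, Recruitment): "around 30-40 stroke participants can be recruited into an intensive imaging study over a 1 year period".
- Training (Section 5.b): "Participants will partake in 1 hour-long exercise sessions, three-times per week, for 8 weeks", that is 3 x 8 = 24 one-hour sessions each.
- Longest reporting interval: 12 months (Section 7.b).

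**Step 1. The plan's own pace.** 120 / 3 years = 40 per year, the top of the stated 30 to 40. At 30 per year, 120 / 30 = 4 years, longer than the planned period. I therefore use 40 as the planned pace and 30 as the low end.

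**Step 2. Longest wait.** For an event just after an annual report, the number randomised before the next one is pace x 1 year:
- 40 per year: 40 / 120 = 33%, about 20 per arm.
- 30 per year: 30 / 120 = 25%, about 15 per arm.

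**Step 3. Mean wait.** If events fall evenly over the reporting year, the mean wait is 6 months:
- 40 per year: 40 x 0.5 = 20, and 20 / 120 = 17%.
- 30 per year: 30 x 0.5 = 15, and 15 / 120 = 12.5%.

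**Step 4. Randomised and fully trained within the longest wait.** With even accrual, those who also finish 8 weeks inside a 52-week interval number pace x (52 - 8) / 52:
- 40 per year: 40 x 44 / 52 = 33.8, or 28% of 120.
- 30 per year: 30 x 44 / 52 = 25.4, or 21% of 120.

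**Step 5. Training volume in the longest wait.** At 40 per year, one year's recruits account for 40 x 24 = 960 session-hours over both arms, of which 20 x 24 = 480 are in the Physical fitness arm.

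**Step 6. Search for another route.** Section 7.b (from the definitions to follow-up of events), Section 7.c on withdrawals and the risk text in 7.a contain no expedited report, no time limit for the investigator or the causality assessor, no notice between sites, and no safety board or independent monitor. Section 7.b refers to an SAE form but does not say to whom it goes or by when.

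**The case against.** **The Statement of Compliance.** It binds the study to the conditions of ethics approval and to named national and good-practice guidance. If those demand faster reporting, the study is already bound to it, and the fault is one misleading sentence and no real delay. This stands as a limit: the approval conditions are not in the document, so the claim is about what Section 7.b says. A sentence that conflicted with the approval conditions would still need correcting.

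**Nothing stops the investigators from acting.** They hear of events quickly, and no text bars them from pausing or amending the trial. This also stands. That participants would go on being randomised is a possibility under the written rule and cannot be taken as certain.

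A reader might draw three stronger conclusions, which the protocol does not support:
- *That the exercise is unattended or that events go unseen.* Live video supervision, study partners where needed, enquiry at each session and review by the investigator and a blinded assessor rule this out. The gap concerns only those outside the team.
- *That one exercise-related cardiac event would contradict the protocol's risk figures.* For people with heart disease, Section 7.a says "an event can occur on average of once in 62,000 hours". Training totals 120 x 24 = 2,880 hours, so the expected count is 2,880 / 62,000 = 0.046, and the chance of at least one event is 1 - exp(-0.046) = 4.5%. The exact 95% Poisson interval for one observed event, 0.025 to 5.57, includes 0.046. The hours also leave out the exercise tests, and the rates are not specific to stroke. One event would deserve attention but would not refute the quoted rate.
- *That the definition of expectedness hides events.* It is tied to the participant's condition and takes no account of the exercise, which is a poor reference. At present it delays nothing, because all SAEs follow the same annual rule whatever their grade.

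**Conclusion.** The point holds in a limited form. As written, Section 7.b allows outside review of an SAE related to the study exercise to wait up to 12 months, and the causality grade does nothing to shorten this. In the longest wait, 30 to 40 participants (25% to 33% of 120) could be randomised. At the mean wait it is about 20 (17%) at 40 per year. A third is thus a worst case, and it refers to randomisation; those both randomised and fully trained in the interval come to 21% to 28%.

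These figures assume even accrual, randomisation at the same pace as recruitment, a fixed annual report date, and, for the mean, events spread evenly over the year. They also assume that no faster duty exists in approval conditions or in a separate safety procedure, neither of which the protocol describes. The change is worth making because it is cheap and bears on participant safety. It does not call the trial's design or its main analysis into question.

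**What to change.** In Section 7.b, keep the annual listing of all SAEs and add one rule. Any SAE graded possibly, probably or definitely related to the study exercise or the exercise test, or occurring during either, is reported promptly to the Ethics Committee and to all site investigators, on the committee's own expedited timeline. The protocol should state that timeline and give the causality assessor a deadline that fits it.

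If the approval conditions already contain such a duty, reword the annual-report sentence to agree with them. If expectedness is then used to decide what is reported quickly, define it against the exercise risks set out in Section 7.a and no longer against the participant's underlying condition.

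The cost is a wording amendment and a few extra letters. The grading is already planned, so no new assessment or staff is needed.
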